**Fig. 2 Fig2:**
[figure not shown]
Schedule of enrolment, interventions, and assessments

## Endpoints

### Primary endpoint

The primary endpoint is time to developing a new Category 2 or above PU from randomisation to 30 days from the end of the treatment phase (maximum of 90 days).

### Secondary endpoints

The secondary endpoints will be determination of the following:Time to developing a PU of Category 3 or above from randomisation to trial completionTime to developing a PU of Category 1 or above from randomisation to trial completionTime to healing of pre-existing Category 2 PUs from randomisation to trial completionHealth-related quality of life using SF-12 and PU-QoL-P instrumentsIncremental cost-effectiveness of APM compared to HSF from the perspective of the health and social care sectors using EQ-5D-5L and health and social care resource utilisation questionnaireMattress changes during the treatment phaseAdverse events

### Skin assessments

Skin will be assessed by trained CRNs/RHCPs using the international PU classification (NPUAP/EPUAP 2014). At baseline and each visit post randomisation, all skin sites at risk of PU development (sacrum, right and left buttocks, hips, heels and elbows), will be assessed by the CRN/RHCP and confirmed as normal skin (0), incontinence-associated dermatitis (IAD), alteration to intact skin (A) or the presence of a PU. PUs when present will be classified and recorded using the National Pressure Ulcer Advisory Panel/European Pressure Ulcer Advisory Panel (NPUAP/EPUAP) classification as Category 1–4 or unstageable [6]. Reasons will be recorded for skin sites that are unable to be assessed.

### Blinding

As it is not possible to blind patients or the TVT, a validation substudy, using photography with blinded central review and expert clinical assessment of the skin sites by an independent member of the team, will be conducted to assess any bias in the reporting of Category 2 or above PUs. Two approaches are being implemented: To assess the risk of over-reporting of the ulcer, the CRN/RHCP who is not independent will photograph each Category 2 or above PU at first observation. To assess risk of under-reporting, 10% of patients are randomised for expert clinical assessment and photography of two skin sites by an independent member (if the patient has at least one PU then a photograph will be taken at a maximum of one PU skin site and one healthy skin site). A standardised photography process will be implemented to ensure a consistent approach is used across all centres when taking and transferring photographs; the central blinded review of the photographs will be undertaken by expert clinical nurse specialists.

### Sample size

A maximum of 588 events i.e. patients developing a new Category 2 or above PU, corresponding to 2954 patients, are required for the study to have 90% power for detecting a difference of 5% in the incidence of Category 2 or above PUs between APM and HSF, assuming an incidence rate of 18% on APM [13, 23] and 23% on HSF [15, 16, 23, 24] (corresponding to a hazard ratio of 0.759), two-sided significance level of 5%, and accounting for 6% loss to follow-up [13].

The PU incidence for APM of 18% was estimated on the intention-to-treat (ITT) population for the completed PRESSURE trial [13], the PURPOSE Pain Cohort study [15, 16] and the trial reported by Vanderwee [23], and hence the sample size estimate incorporates the effect of any non-compliance. The sample size accounts for multiplicity in the interim analyses using Lan-DeMets α and β spending functions [25].

PU incidence rates cannot be estimated accurately for the HSF and the maximum sample size estimate is based on the detection of the smallest clinically relevant difference of 5% (clinical opinion). If the difference is >5% then the trial will have sufficient power to stop early having demonstrated superiority (or inferiority) of the APM; if the difference is <5% then the trial is likely to stop early for futility.

The approximate sample size for the PUQoL-P substudy will be 500 patients.

A maximum of approximately 1653 photographs are expected for the central blinded review, which will enable kappa to be estimated to within a precision of at least ±0.044 (corresponding to the half width of the 95% CI), assuming 65% of photographs are of Category 2 or above PUs and kappa ≥0.5.

### Statistical analysis

Statistical analysis plans for the interim and final analyses will be finalised and signed off before any data analyses are conducted.

All analyses will be on an ITT basis where patients will be analysed according to treatment group randomised to receive. A per protocol population will also be defined, which will include all eligible randomised patients according to the treatment received but will exclude major protocol violations as agreed by the clinical members of the Trial Management Group (TMG).

### Interim analysis and stopping rules

The group sequential design provides an efficient design through the possibility of early stopping ([26, 27]

As this is a group sequential design, the trial will have a maximum of three planned analyses with unequally spaced reviews at event-driven coherent cut-points:The first analysis conducted after 300 events corresponds to the earliest time point at which the trial can be stopped for demonstrating overwhelming evidence of efficacy or futility, and also corresponds to the minimum number of events required for conducting the economic evaluation. The futility boundaries are constructed as non-binding in order for the Data Monitoring and Ethics Committee (DMEC) to overrule a decision of stopping early for futility in the event that a futility boundary is crossed. In the event of the DMEC recommending that the trial is stopped for futility using the pre-defined stopping criteria, an expected value of sample information analysis will be undertaken to assess the value of additional sample information on the effectiveness parameter, to establish whether continuing the trial would be valuable from the NHS decision-makers’ perspective. If the decision to stop is overruled, the stopping boundaries will be adjusted using the “buy-back alpha” approach [28].The second analysis, conducted after 445 events corresponds to the number of expected events required for trial termination under futility (with 434 corresponding to the number of events required for demonstrating superiority or inferiority of APM to HSF).The final review will be conducted after 588 events have occurred.

The double triangular group sequential design is shown in Fig. 3. The efficacy and futility stopping boundaries are defined using Lan-DeMets α and β spending functions, which provide conservative stop/continue criteria at the interim analyses.

**Fig. 3 Fig3:**
[figure not shown]
Double triangular group sequential design

At each interim analysis, the primary analysis of the primary endpoint, time to developing a Category 2 or above PU, will be conducted on both the ITT and per protocol population. The test statistic for the treatment effect from the Cox proportional hazards model (after confirming the proportional hazards assumption is valid), adjusting for the minimisation factors and covariates specified in the primary endpoint analysis section below, will be used to test for a difference between treatment groups. The hazard ratio for the treatment effect and adjusted confidence interval corresponding to the nominal *p* value will be presented.

Interim analyses will be presented to the DMEC who will then advise the Trial Steering Committee (TSC) if there is proof beyond reasonable doubt that the trial should be stopped in accordance with the planned stopping rules.

### Primary endpoint analysis

#### Primary analysis

A Cox proportional hazards model (after confirming the proportional hazards assumption is valid) will be fitted to the primary endpoint, with adjustment for the minimisation factors: healthcare setting, PU status and consent, and the following covariates: presence of pain on a healthy, altered or Category 1 PU skin site, conditions affecting peripheral circulation and treatment group. Centre will be assessed for inclusion as a random effect. The hazard ratio for the estimate of the treatment effect and adjusted confidence interval corresponding to the nominal *p* value will be presented. Patients who do not develop a Category 2 or above PU during the treatment phase or by 30 days post treatment follow-up will be censored at the date of their last evaluable skin assessment.

Kaplan-Meier estimates of the probability of patients developing a Category 2 or above PU over 90 days in each group and adjusted confidence intervals corresponding to the nominal *p* value will be presented.

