### Study population

The multicentre trial will be conducted in acute secondary care hospitals, community hospitals and NHS-funded intermediate care/rehabilitation facilities in England and Scotland. All participating centres have Tissue Viability Nurse Specialists in post with hospital-wide remits to establish pressure ulcer prevention guidelines, policies and practice. Patients with evidence of acute illness will be assessed for eligibility in accordance with the criteria in Table 1.

**Table 1 Tab1:** Inclusion and exclusion criteria

Inclusion criteria
1. Evidence of acute illness through:
a. acute admission to secondary care hospital, community hospital or NHS-funded intermediate care/rehabilitation facility
b. secondary care, community hospital or NHS-funded intermediate care/rehabilitation facility in-patient with onset of acute illness secondary to elective admission
c. recent secondary care hospital discharge to community hospital or NHS-funded intermediate care/rehabilitation facility
2. Aged ≥ 18 years
3. Have an expected total length of stay of 5 or more days
4. At high risk of PU development due to one or more of the following:
a. bedfast/chairfast AND completely immobile/very limited mobility (Braden activity score 1 or 2 and Mobility score 1 or 2) [20]
b. Category 1 PU on any pressure area skin site
c. localised skin pain on a healthy, altered or Category 1 pressure area skin site
5. Consent to participate (written informed consent, witnessed verbal consent, consultee agreement (England) or nearest relative/guardian/welfare attorney (Scotland))
6. Expected to comply with the follow-up schedule
7. The patient is on an electric profiling bed frame
Exclusion criteria
1. Have previously participated in the PRESSURE 2 trial
2. Have a current or previous Category ≥3 PU
3. Have planned admission to ICU where standard care is alternating-pressure mattress provision
4. Unable to receive the intervention (for example, sleep at night in a chair or unable to be transferred to randomised mattress)
5. Patient weight is lower or higher than weight limits for HSF and alternating-pressure mattresses (<45 kg/>180 kg)
6. It is ethically inappropriate to approach the patient

*HSF* high-specification foam, *ICU* intensive care unit, *NHS* National Health Service, *PU* pressure ulcer

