### Treatment phase follow-up assessment

Treatment phase follow-up assessments will be undertaken up to a maximum of 60 days post randomisation. These will be undertaken by a trained CRN/RHCP twice weekly from randomisation up to 30 days, then once weekly up to 60 days. The treatment phase is defined as the period from randomisation to discharge, transfer to an ineligible facility, when the patient is considered no longer at high risk (considered at each assessment), reaching 60 days, withdrawal or death, whichever is soonest. No longer at high risk is defined as no Category 1 or above PU on any skin site AND no localised skin pain on a healthy, altered or Category 1 skin site, AND improved mobility and activity (Braden activity score 3 or 4 AND Mobility score 3 or 4) [20].

Patients will have a skin assessment, including pain and photography (if consented) of Category 2 and above ulcers where present and not previously photographed, and PU prevention interventions recorded. Mattress compliance and technical faults will be collected daily. At weeks 1 and 3 post randomisation*,* healthcare resource utilisation, and quality of life questionnaires SF-12 [21], PUQoL-UI and EQ-5D-5L [22] will be completed (PUQoL-UI and EQ-5D-5L by proxy for patients lacking consent); the PU-QoL-P will again be administered to a subset of patients.

Following the end of the treatment phase patients will receive care in line with routine standard practice.

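### The primary Cox model adjusts for two of the three entry risk criteria but not for immobility, which is recorded at baseline; a small gain in efficiency is forgone

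*Protocol article*

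**What the plan says.** Table 1 of the protocol article (Study population) introduces inclusion criterion 4 with "At high risk of PU development due to one or more of the following". The three alternatives are:

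- 4a: "bedfast/chairfast AND completely immobile/very limited mobility (Braden activity score 1 or 2 and Mobility score 1 or 2"
- 4b: "Category 1 PU on any pressure area skin site"
- 4c: "localised skin pain on a healthy, altered or Category 1 pressure area skin site"

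Under Primary analysis, the Cox model is specified with "adjustment for the minimisation factors: healthcare setting, PU status and consent, and the following covariates: presence of pain". The list closes with "conditions affecting peripheral circulation and treatment group". On the remaining minimisation factor, the text says "Centre will be assessed for inclusion as a random effect". No activity or mobility term appears.

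The Baseline assessment section has the Braden scale and PURPOSE-T completed, including activity and mobility status. Neither is among the minimisation factors under Randomisation. The section on interim analysis and stopping rules takes its covariates from the primary analysis, and the secondary analysis section uses the same set for the Category 1 and Category 3 endpoints.

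**The concern.** The protocol's own definition of high risk rests on three characteristics, and the model carries two of them. The third can differ between patients, because someone who enters through 4b or 4c may be mobile. It is balanced neither by minimisation nor by the model, although the data are collected anyway.

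In a Cox model, leaving out a prognostic baseline variable pulls the estimated treatment hazard ratio slightly towards 1 relative to the ratio conditional on that variable, without a compensating gain in precision. Including it would therefore raise power somewhat at the same number of events. Because one covariate list serves every look and two secondary endpoints, the choice is repeated throughout the trial.

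**Working it through.** **Inputs from the protocol article.** Incidence 18% on APM and 23% on HSF, hazard ratio 0.759, 90% power, two-sided 5%, maximum 588 events (Sample size); 1:1 allocation (Randomisation); 554 events for a fixed design (Discussion).

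**Inputs assumed.** Prevalence of immobility 0.3 to 0.85 and its hazard ratio 1.5 to 4. The documents give neither.

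**Step 1: reproduce the plan's figures.** The hazard ratio is ln(1 − 0.18)/ln(1 − 0.23) = ln(0.82)/ln(0.77) = 0.7593. Schoenfeld's formula gives events = 4(1.960 + 1.282)²/(ln HR)². This is 553 at 0.759 and 555 at 0.7593, in line with the stated 554. The group sequential inflation is 588/554 = 1.061.

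**Step 2: what the 90% rests on.** The two incidences are averages over all patients, mobile and immobile. The hazard ratio of 0.759 derived from them is therefore marginal with respect to mobility. No gain from covariates enters the calculation.

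**Step 3: power without and with the covariate.** The overall incidences were held at 18% and 23%, and exponential hazards were assumed with one binary prognostic covariate and 554 events. The large-sample power of the unstratified log-rank test (covariate omitted) was compared with that of the log-rank test stratified by the covariate (covariate adjusted).

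| Assumed HR of immobility | Power, omitted | Power, adjusted | Gain (points) | Equivalent events |
|---|---|---|---|---|
| 1.5 | 89.7–89.8% | 89.8–90.0% | 0.1–0.3 | 2–5 |
| 2 | 89.8% | 90.0–90.5% | 0.3–0.8 | 5–15 |
| 3 | 89.8% | 90.2–91.8% | 0.5–2.0 | 9–39 |
| 4 | 89.8–89.9% | 90.4–93.0% | 0.6–3.1 | 12–63 |

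Ranges run over prevalence 0.3 to 0.85. Equivalent events are 554 × (1 − 1/r), where r is the squared ratio of the adjusted to the omitted expected z statistic. For prevalence 0.3 and hazard ratio 2, r = 1.0274, so 554 × (1 − 1/1.0274) ≈ 15. The omitted column barely moves because the overall incidences are fixed.

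**Step 4: simulation check.** With 6000 runs per scenario and 2703 patients (554/0.205), power omitted versus adjusted was:

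- prevalence 0.5, hazard ratio 2: 90.2% versus 90.7%
- prevalence 0.5, hazard ratio 3: 90.2% versus 91.9%
- prevalence 0.5, hazard ratio 4: 90.3% versus 92.6%
- prevalence 0.7, hazard ratio 2: 89.7% versus 90.1%

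**Step 5: overlap.** The comparison contains no other covariates, whereas the real model already holds ulcer status and pain. Since one of 4a to 4c is required, every patient with neither a Category 1 ulcer nor skin pain must be immobile. Mobility therefore adds information only among patients who have one of those features, and the true gain is probably below the table's figures.

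**The case against.** The strongest objection is that nothing here is an error. The article does not promise that every entry criterion will be a covariate. A short, pre-specified list is a legitimate choice, and its rationale may sit in the full protocol or analysis plan. That stands as far as it goes: there is no contradiction, and a missing rationale is not the complaint. The complaint concerns a list that the article fixes.

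A reader might infer that the trial loses power against its plan. If 0.759 is read as the hazard ratio conditional on mobility, and immobility has a hazard ratio of 2 and a prevalence of 30–70%, the attenuation would be worth about 10–16 of the 588 events. The documents do not support that reading, because 0.759 comes directly from the two overall incidences.

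A reader might also infer that the omission undermines independent censoring, because leaving the treatment phase as no longer at high risk requires "improved mobility and activity (Braden activity score 3 or 4 AND Mobility score 3 or 4". This is at most a supporting reason. That exit depends on current mobility, judged at each assessment, together with the absence of ulcers and pain, and it is one of several exits. A final skin assessment is planned 30 days after exit. Bias under no treatment effect would need exit to differ by arm, which is an assumption, and a baseline term would remove only part of it.

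**Conclusion.** The point holds as a modest improvement to the analysis. The model covers ulcer status and pain but not immobility, although activity and mobility are recorded at baseline. The planned 90% power stands. The forgone gain is about 0.1–0.8 points if immobility has a hazard ratio of 1.5 to 2, and about 0.5–3.1 points at 3 to 4, in each case less any overlap with covariates already modelled. These sizes depend on assumed prevalence and prognostic strength, exponential hazards and a binary covariate. Nothing in the documents shows that the omission invalidates the primary test.

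**What to change.** Add baseline Braden activity and mobility to the fixed covariate list under Primary analysis, either as the two scores or as a yes/no indicator for criterion 4a. The interim tests and the Category 1 and Category 3 models then take it up by reference. Fix the form of the term in the analysis plan before any unblinded comparison.

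The cost is one or two more model terms, with no new data collection. The reported hazard ratio would also be conditional on mobility; under the scenarios above it would lie between 0.746 and 0.759.

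Timing is the real constraint. The first look is at 300 events, which at the planned ratio corresponds to 300 × 2954/588 ≈ 1507 patients, and Trial status reports 1501 randomised by 13 April 2016. The article does not give the number of events observed. If the first look has already taken place under the published list, the primary model should be left as it is and the mobility-adjusted model reported as a sensitivity analysis.

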#### Moderator and mediator analyses

Potential predictors of time to developing Category 2 or above PU will be explored by assessing potential predictor by treatment group interactions in the model. In addition, the relationship between potential moderator and mediator variables (including length of stay, time on allocated mattress, patient turning, and use of specialist cushions, heel protectors and protective dressings) and treatment effect will be modeled.

#### Secondary endpoint analysis

The secondary endpoints, time to developing a PU of at least Category 1, and time to developing a PU of at least Category 3, will be analysed using Cox proportional hazards modelling (after confirming the proportional hazards assumption is valid) adjusting for the minimisation factors and same covariates as for the primary endpoint analysis and treatment group.

A Cox proportional hazards model (after confirming the proportional hazards assumption is valid) will be fitted to the outcome time to healing of pre-existing Category 2 PUs; covariates fitted in the primary endpoint model will be assessed for inclusion and treatment group.

A substudy analysis will be performed to examine the PU-QoL-P instrument responsiveness; effect sizes [29] and standardised response means (SRM) [30] before and after mattress allocation will be estimated. Independent *t* tests will be conducted to assess the ability of the PU-QoL-P instrument to distinguish between patients whose PUs deteriorate or heal. Subject to the results of the instrument responsiveness analysis, QoL domains and subscales for the SF-12 and PU-QoL-P will be compared between treatment groups using multilevel repeated measures modeling allowing for time, mattress type, mattress type by time interaction, adjusting for baseline QoL, patient and patient by time interaction as random effects.

Adverse events and serious adverse events classified as related to the mattress, resulting from administration of any research procedures, and falls and device-related events during the treatment phase and follow-up will be listed and summarised by treatment group.

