## Assessments/data collection and follow-up

### Baseline assessment

Patient demographic information including NHS number, date of birth, gender, date of admission, type of admission, category of medical condition (orthopaedics and trauma, oncology, critical care and other conditions) and ethnicity will be recorded.

Patient risk profiles and key risk factors will be recorded through clinical assessment and completion of the Braden scale and PURPOSE-T including baseline skin status, localised skin pain on pressure areas, activity and mobility status, sensory perception, diabetes, conditions affecting macro and micro circulatory function, nutrition, skin moisture, friction and shear, PU history, height and weight (self-report or notes where available) and duration and size of ulcer and photograph (if consented) for patients with a pre-existing category 2 PU [9, 15, 16, 18].

PU prevention interventions pre-randomisation will be recorded including mattress type, turning frequency and seating provision.

Patients will be asked to complete quality of life questionnaires, which include: 12-item Short Form (SF-12), Pressure Ulcer Quality of Life-Utility Index (PUQoL-UI) [15] and EuroQol-5D 5 level (EQ-5D-5L); with the latter two by proxy for patients who lack capacity. In addition PUQoL-Prevention (P) data, an adapted version of PUQoL [19], will be collected in a subset of patients.

It is expected that the baseline assessment and randomisation will take place on the same day.

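### The healing model borrows its covariates from the new-ulcer model, leaves their inclusion open, and does not list the baseline ulcer size and duration recorded for these patients

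*Protocol article*

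**What the plan says.** All references are to the protocol article.

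- **Healing model (Secondary endpoint analysis).** A Cox model is fitted to time to healing of pre-existing Category 2 ulcers. On adjustment: "covariates fitted in the primary endpoint model will be assessed for inclusion and treatment group". No criterion for inclusion is given.
- **Category 1 and Category 3 endpoints (same section, paragraph before).** Here the set is fixed: "adjusting for the minimisation factors and same covariates as for the primary endpoint analysis and treatment group".
- **The list being borrowed (Primary analysis).** The model is fitted "with adjustment for the minimisation factors: healthcare setting, PU status and consent", plus "presence of pain on a healthy, altered or Category 1 PU skin site, conditions affecting peripheral circulation and treatment group". On centre: "Centre will be assessed for inclusion as a random effect".
- **What is recorded at entry (Baseline assessment).** The items include "duration and size of ulcer and photograph (if consented) for patients with a pre-existing category 2 PU". No section gives ulcer size or duration a role in the healing analysis.
- **Later documents (Statistical analysis).** "Statistical analysis plans for the interim and final analyses will be finalised and signed off before any data analyses are conducted".

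**The concern.** The candidates for the healing model were chosen for another question, namely which patients develop a new ulcer. The healing analysis is confined to patients who already have a Category 2 ulcer. For them the list contains one item that cannot vary and one that is defined to leave out the ulcer under study. It omits the two baseline measurements that describe that ulcer.

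Two things are at stake. First, if ulcer size and duration are prognostic for healing, a model without them tests the mattress effect less sensitively and estimates a hazard ratio nearer 1. Randomisation is minimised on PU status but not on size or duration, so chance differences between arms in these measurements are neither prevented by design nor allowed for in the analysis. Second, an adjustment set left open for a treatment comparison in an open-label trial leaves room for choosing among models, which the fixed sets for the neighbouring endpoints avoid.

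**Working it through.** **1. The plan's own figures.** No patient number, healing rate, effect size or power is stated for healing. The power statement, "90% power for detecting a difference of 5% in the incidence of Category 2 or above PUs", concerns new ulcers only. The fixed-design figure of 554 events (Discussion) does reproduce: HR = ln(1 − 0.18)/ln(1 − 0.23) = 0.759, and Schoenfeld's formula 4(1.960 + 1.282)²/(ln 0.759)² gives 553 (555 with the unrounded HR). It has no bearing on healing.

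**2. Each listed covariate within the healing subset.**

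| Covariate in the primary model | In patients with a Category 2 ulcer at entry |
|---|---|
| Healthcare setting, consent method | Can vary |
| PU status | Levels are none, Category 1 and Category 2 (Randomisation), and Category 3 or above is excluded (Table 1); constant |
| Pain | Covers healthy, altered or Category 1 sites; not the Category 2 site |
| Peripheral circulation | Can vary |
| Centre | Possible random effect, left open in the primary model too |
| Ulcer size, ulcer duration | Recorded at baseline; not listed |

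**3. What omission could cost.** The documents supply no inputs, so all of these are assumptions: 1:1 allocation, exponential healing times, a common censoring time, and one normal baseline score standing for size and duration together. The score has SD s on the log-hazard scale, so one SD changes the healing hazard by exp(0.3) = 1.35, exp(0.5) = 1.65 or exp(0.8) = 2.23. There were 3,000 simulated trials per setting, giving a Monte Carlo standard error of at most √(0.25/3000) = 0.9 points. Entries are power without → with adjustment for the score.

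| s | 200 patients, 140 healings, HR 1.6 | 400 patients, 280 healings, HR 1.45 | 200 patients, 100 healings, HR 1.6 | Loss (points) |
|---|---|---|---|---|
| 0 | 76.8 → 77.4% | 87.1 → 87.0% | 63.0 → 63.4% | about 0 |
| 0.3 | 75.7 → 78.5% | 83.7 → 86.6% | 62.1 → 64.1% | 2–3 |
| 0.5 | 72.3 → 79.5% | 79.6 → 87.1% | 58.0 → 64.0% | 6–8 |
| 0.8 | 58.2 → 79.8% | 69.2 → 88.0% | 49.4 → 64.3% | 15–22 |

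As a check on the s = 0 row, Schoenfeld's approximation Φ(√d · ln HR/2 − 1.96) gives 79%, 87% and 65% for the three columns, close to the simulated values.

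**4. Estimated hazard ratio.** At s = 0.8 the mean estimate without and with the score was 1.45 against 1.61 (140 healings), 1.34 against 1.46 (280) and 1.49 against 1.61 (100). At s = 0.3 the first of these was 1.57 against 1.60.

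**5. Type I error.** With HR = 1, 400 patients and 280 healings, rejection rates without and with the score were 5.1% and 5.2% (s = 0.5), and 5.3% and 4.8% (s = 0.8).

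**The case against.** The strongest reply is that a condensed article may leave the covariates of one secondary endpoint to an analysis plan that is signed off before any analysis. That plan is not shown, could fix the set, and could add size and duration, since nothing in the article forbids them. This stands as far as it goes. But the article is not silent: it names a source list and an open inclusion step, and a plan that followed it would omit both measurements.

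Four further objections stand and limit the point.

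- A reader might infer that covariates will be picked by looking at the outcome data. The article states no selection method. The assessment could rest on clinical relevance or on the number of healings, and the candidate list is itself stated in advance.
- A constant PU status term does no harm, because it drops out of a Cox model. Assessing the covariates may be the very step meant to remove it. The term shows that the list fits the subset poorly, not that the estimate is damaged.
- A reader might infer that omission biases the comparison. Under randomisation, chance imbalance adds variability, not systematic bias, and the test keeps its 5% level. Much of the shift in hazard ratio reflects non-collapsibility: the adjusted and unadjusted Cox hazard ratios are different quantities.
- No section says that size or duration predicts healing of a Category 2 ulcer, so the power loss is conditional.

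**Conclusion.** The point holds as a weakness in a stated method for a secondary endpoint. The candidate list does not suit the healing subset, inclusion is left open where the neighbouring endpoints have a fixed set, and two baseline measurements already collected for these patients go unused.

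The documents cannot say what this costs. Over the assumed settings the loss of power runs from nothing to about 22 points, depending mainly on how strongly size and duration predict healing beyond the other covariates; which case applies is unknown. A definite loss of power is therefore not supported. The healing endpoint does not enter the stopping rules, and the primary conclusion is unaffected. The case for change rests on its low cost.

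**What to change.** Before any analysis by randomised group, state the healing model in full:

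- Fix the covariates as treatment, baseline ulcer size (for example log area), baseline ulcer duration, healthcare setting and consent method, with centre handled as in the primary model.
- Omit PU status.
- Decide in advance whether pain and peripheral circulation stay in.
- State which ulcer's size and duration are used when a patient has more than one Category 2 ulcer at entry.
- Remove the open inclusion step.

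This needs a change of wording and no new data collection. The one small downside is that patients with missing baseline size or duration need a simple imputation of that value, whose method should be named at the same time.
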